### Planned Analysis

#### Study One: Development Phase

Focus groups and interviews will be recorded and transcribed verbatim. They will then be analyzed using thematic analysis. Themes will give an understanding of what young people, parents and carers, and clinicians think of the content and format of Power Up. Further developments to the app will be made in response to these themes.

#### Study Two: Feasibility Testing Phase

Descriptive statistics will be used to characterize the participants in terms of sociodemographic profile. The primary outcome measure of the feasibility trial, the standard deviations and intraclass correlation coefficients of the shared decision-making measures, will identify the parameters to enable planning for the subsequent trial. These will be used to calculate the sample size for the future planned cluster controlled trial. In addition, the acceptability of studying Power Up in a cluster controlled trial will be examined using recruitment and retention rates, number of sessions attended, and number of individuals who refuse treatment. The feasibility of studying Power Up will be indicated by the number of patients failing to comply with the full clinical/research protocol and qualitative information obtained from the posttrial interviews with clinicians and young people.

The secondary outcome measures, an initial indication of the impact that Power Up may have on a young person’s clinical outcomes, are ­­­the change in patient activation, empowerment, and SDQ scores pre- and postintervention. Qualitative information regarding the impact of Power Up will also be obtained from the posttrial interviews with clinicians and young people.

The results of this study will clarify the feasibility and acceptability of studying Power Up in a prospective cluster controlled trial. In addition, the results will highlight the possible utility and challenges of implementing Power Up with young people in CAMHS.

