### Study Two: Feasibility Testing Phase

#### Participants and Design

In the feasibility testing phase, young people’s experiences of CAMHS while using Power Up will be compared to young people’s experiences of CAMHS without using the app. Study 2 is designed as a feasibility trial using a waitlist control design. A total of 60 young people, who are aged 11 to 19 years old, have recently been referred to CAMHS, and are presenting with emotional difficulties will be recruited to the trial. A clinician will have confirmed that the young person does not have any vulnerability that would make taking part in the study inappropriate to their context. They will also understand English well enough to provide informed consent or assent if they are younger than 16 years old. First, 30 young people will be recruited to the control phase of the trial where they will receive management as usual. Subsequently, 30 different young people will be recruited to the intervention phase of the trial where they will be given Power Up to use alongside management as usual.

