#### Procedure

Participants will be recruited in 7 to 10 London CAMHS sites. Clinicians will identify young people who are in their initial sessions in CAMHS. Young people and their parent or carer will be given information about the trial, and they will indicate to a member of CAMHS staff or the research team, through a telephone or face-to-face conversation, that they are interested in taking part in the project. For the control phase and the intervention phase, each service will be required to recruit 5 to 10 young people (for a total of 30 young people across services for each phase). This initial contact by services and subsequent recruitment by researchers will replicate the processes described in study 1.

If the young person is recruited during the control phase, they will meet with a researcher, along with their parent or carer, at a convenient time and place in the early stages of their therapy (up to the third treatment session). The researcher will take informed consent using the same procedures as described in study 1. The young person will then complete a battery of measures that take an estimated 15 minutes to complete. The young person’s parent or carer and clinicians will also complete a short questionnaire each.

Three months later all participants will be recontacted by the researchers and a time will be arranged for them to complete the same battery of measures a second time. Their clinician will also be asked to report the young person’s presenting problems, type of interventions used, number of sessions attended, number of missed appointments, and length of appointments.

Data collection for the intervention phase will replicate the control phase procedures. For those recruited to the intervention phase, the researcher will also help the young person to download Power Up onto their phone and will talk them through its functions after completing the first time measures. The young person will then be able to use Power Up as much as they want throughout their therapy at CAMHS, within and between sessions. In the intervention phase, a total of 10 to 12 young people and 10 to 12 clinicians across services will also take part in a posttrial interview where they will be asked about their experiences of and opinions on using Power Up in CAMHS.

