## Results

Funding has been secured from the National Institute for Health Research (NIHR)–Central Commissioning Facility to cover the full length of the project. Interviews were completed for study 1 in December 2016. The project is currently in the control phase of the feasibility trial, and 10 CAMHS sites have been recruited to take part in the study. The intervention phase of the feasibility trial commenced in June 2017. It is anticipated that data collection will be completed by December 2017.

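### Sixty young people in 7 to 10 sites cannot pin down the ICC that the plan says will be used to size the later cluster trial

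*Protocol article*

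**What the plan says.** The Planned Analysis for Study Two names as primary outcome "The primary outcome measure of the feasibility trial, the standard deviations and intraclass correlation coefficients of the shared decision-making measures". It says that these will establish the parameters needed to plan the later trial, and then: "These will be used to calculate the sample size for the future planned cluster controlled trial".

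The amount of data is fixed elsewhere in the article. Study Two, Participants and Design: "A total of 60 young people, who are aged 11 to 19 years old", 30 in a control phase and then 30 different people in an intervention phase. Procedure: "Participants will be recruited in 7 to 10 London CAMHS sites", with "for a total of 30 young people across services for each phase". The Results section reports that "10 CAMHS sites have been recruited to take part in the study".

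The article states no expected ICC, no target precision, and no source for the figure of 60.

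**The concern.** Information about an ICC comes mainly from the number of clusters and, when clusters are small, also from their size. Here both are small: 6.0 to 8.6 people per site over both phases, and 3.0 to 4.3 per site within one phase. The parameter that drives the inflation of a cluster trial's sample size would be taken from data that hardly constrain it.

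The quality of the next trial's sample size is at stake. If the estimate falls at or below zero by chance and is taken at face value, the later trial gets no inflation for clustering and is underpowered. If it falls high by chance, the required size is exaggerated several-fold. Because the ICC is part of the primary outcome and the sample size calculation is its stated use, this bears on a central product of the study.

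**Working it through.** The article gives no derivation of 60 and no precision target, so there is no planned figure to reproduce. The check asks what precision the stated design delivers.

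**Inputs from the article.** N = 60 (Participants and Design). k = 7 to 10 sites (Procedure), with 10 reported in Results. Mean site size m = 60/7 = 8.57 or 60/10 = 6.0. The Procedure also asks for 5 to 10 recruits per service per phase, which over 7 to 10 services gives 7 × 5 = 35 to 10 × 10 = 100 per phase and does not match its own total of 30. The fixed total of 60 is used here.

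**Assumptions.** True ICC ρ: not given, shown from 0.01 to 0.20. Loss to follow-up: not given, 20% (N = 48) shown as a sensitivity. Cluster size in the later trial: not given, 20 assumed.

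**Method.** One-way random-effects ANOVA with equal site sizes and F = MSB/MSW.
- Estimate: ICC = (F − 1)/(F + m − 1). An estimate r corresponds to F = 1 + m·r/(1 − r).
- Exact 95% interval: divide F by the 97.5% and 2.5% points of F(k − 1, N − k) and convert each result back to an ICC.
- Chance of an estimate ≤ 0: P[F(k − 1, N − k) ≤ 1/(1 + mρ/(1 − ρ))].

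**Interval for an observed 0.05, 10 sites.** F = 1 + 6 × 0.05/0.95 = 1.316. The 97.5% and 2.5% points of F(9, 50) are 2.381 and 0.288. Lower: 1.316/2.381 = 0.553, so (0.553 − 1)/(0.553 + 5) = −0.08. Upper: 1.316/0.288 = 4.57, so (4.57 − 1)/(4.57 + 5) = 0.37.

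| Observed ICC | 7 sites, 95% CI | 10 sites, 95% CI |
|---|---|---|
| 0.01 | −0.074 to 0.339 | −0.102 to 0.309 |
| 0.05 | −0.056 to 0.420 | −0.081 to 0.373 |
| 0.10 | −0.032 to 0.504 | −0.053 to 0.444 |
| 0.15 | −0.006 to 0.573 | −0.023 to 0.506 |
| 0.20 | 0.021 to 0.631 | 0.008 to 0.561 |

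**Chance of an estimate at or below zero.** For ρ = 0.05 and 10 sites: P[F(9, 50) ≤ 1/1.316 = 0.760] = 0.347.

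| True ICC | 7 sites, N = 60 | 10 sites, N = 60 | 10 sites, N = 48 |
|---|---|---|---|
| 0.01 | 0.512 | 0.503 | 0.508 |
| 0.05 | 0.341 | 0.347 | 0.380 |
| 0.10 | 0.204 | 0.209 | 0.254 |
| 0.20 | 0.075 | 0.071 | 0.105 |

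**Sensitivity.** Removing the phase mean leaves the figures at ρ = 0.05 unchanged (0.341 and 0.347). Simulated unequal site sizes give 0.35. With N = 48 and 10 sites, an observed 0.05 has an interval of −0.11 to 0.41. Within one phase (N = 30, 10 sites) the interval is −0.25 to 0.52 and the chance of an estimate ≤ 0 at ρ = 0.05 is 0.43.

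**Consequence for the later trial (20 per cluster assumed).** Design effect = 1 + 19 × ICC: 1.00 at ICC 0, 1.95 at 0.05, and 1 + 19 × 0.373 = 8.1 at the upper limit. If the trial is planned for 90% power at ICC 0 and the truth is 0.05, power = Φ((1.96 + 1.282)/√1.95 − 1.96) = Φ(0.36) = 0.64.

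**SD for comparison.** With 58 degrees of freedom the 95% limits are 0.85 to 1.22 times the estimate, which is adequate for planning.

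**The case against.** The strongest reply is that the article does not say how the ICC will enter the calculation. A reader might infer that the single estimate will be inserted directly, with no interval and no outside evidence. The text does not say that. It names the estimates and their use, mentions neither intervals nor outside sources, and rules out neither; the Discussion says more loosely that the findings will inform planning. A condensed article may leave such detail to a fuller document. This stands, and the point is therefore not that a bad method has been declared. What remains is that the article claims the design will establish the ICC. The numbers of sites and participants do not allow that, and no fuller analysis plan can change it.

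A reader might also take the chance of a falsely null ICC to be one in three outright. That holds only near a true ICC of 0.05 with all 60 analysed; the documents give no ICC, and the figure runs from about 1 in 2 to 1 in 14 over the range shown.

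The harm also depends on future planners accepting a zero estimate and applying no inflation, which nothing in the article says they will do. Several shared decision-making measures are planned, so one chance zero need not decide the matter, although having more measures does not make any one ICC precise. Finally, the SDs, recruitment, retention, compliance and interview data are not touched by this point, so it would be wrong to say that the whole feasibility study misleads.

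**Conclusion.** The point holds for the ICC. On the article's own numbers, any observed ICC from 0.01 to 0.15 has a 95% interval that includes zero and extends to at least about 0.31. That leaves open anything from no inflation to a many-fold inflation of the later trial. The intervals rest only on N = 60, 7 to 10 sites and a standard one-way model with roughly equal sites; loss to follow-up widens them.

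The chance of an estimate at or below zero depends on an assumed true ICC: about 1 in 2 at 0.01, 1 in 3 at 0.05, 1 in 5 at 0.10 and 1 in 14 at 0.20, and more with dropout. The 64% power figure illustrates the risk under three assumptions (20 per cluster, true ICC 0.05, planning at ICC 0) and is not a forecast. The finding does not extend to the SDs.

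**What to change.** In the Planned Analysis for Study Two, replace the sentence on using the estimates for the later sample size with wording such as:

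*ICCs (site as random effect, phase as fixed effect) and SDs will be reported with 95% confidence intervals. The future sample size will not rest on the single ICC estimate or on an estimate truncated at zero. It will be tabulated over a range of ICCs that combines this estimate and its interval with ICCs from comparable outside studies, with a pre-set non-zero floor.*

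In the sentence before it, say that the study will *inform* the ICC rather than *identify* it.

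No extra participants, sites or measures are needed. The cost is a small amount of added analysis and a somewhat larger, less favourable planning figure for the next trial. Making feasibility and acceptability the primary result, or planning on an upper confidence limit for the SD, are optional choices and not part of the required change.

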## Results

Funding has been secured from the National Institute for Health Research (NIHR)–Central Commissioning Facility to cover the full length of the project. Interviews were completed for study 1 in December 2016. The project is currently in the control phase of the feasibility trial, and 10 CAMHS sites have been recruited to take part in the study. The intervention phase of the feasibility trial commenced in June 2017. It is anticipated that data collection will be completed by December 2017.

## Discussion

The trial and its findings will inform the development and implementation of a shared decision-making app for CAMHS. It will be the first of its kind for young people managing emotional problems in the NHS. This will contribute to the growing use of technology to support children and young people with mental health difficulties.

In addition, the findings will inform the planning of a prospective cluster controlled trial. This larger study will give further evidence of the app’s efficacy in promoting shared decision making in CAMHS while reducing missed appointments and increasing positive outcomes. This will also indicate the potential financial savings the app could have for services. It is hoped that this research and the future trial can work toward putting children, young people, and their families at the heart of decision making about their care.

## Appendix

Multimedia Appendix 1 Topic guides.

## Abbreviations

CAMHS: children and adolescent mental health services
CSRI: Client Receipt of Services Inventory–Children’s Version
ESQ: Experience of Service Questionnaire
NHS: National Health Service
NICE: National Institute for Health and Care Excellence
NIHR: National Institute for Health Research
PAM-MH: Patient Activation Measure–Mental Health
PPI: patient and public involvement
SDM Q-9: Shared Decision Making Questionnaire
SDQ: Strengths and Difficulties Questionnaire
YES-MH: Youth Efficacy/Empowerment Scale–Mental Health
